### Study population

A total of approximately 2,340 adults will be enrolled from five participating centers, representing Han, Hui, Tibetan, and Kazakh populations across regions with varying altitude, environmental exposure, and healthcare accessibility. Recruitment targets are prespecified according to catchment characteristics, with planned enrolment of 900–1,050 Han, 650–750 Hui, 400–500 Tibetan, and 250–350 Kazakh participants. Sample size estimation is based on an event-driven approach (Supplementary Material 1). Assuming a 4% cumulative incidence of first AMI over 24 months, approximately 80 events are expected, supporting multivariable modeling and subgroup analyses.

Participants will be eligible if they: (1) are aged 30–85 years; (2) have an estimated 10-year atherosclerotic cardiovascular disease (ASCVD) risk ≥20% (6); (3) are permanent residents of the study area (≥6 months per year); (4) provide written informed consent; and (5) agree to repeated follow-up and biospecimen collection. Exclusion criteria include: (1) major comorbid conditions such as end-stage renal disease, hepatic failure, or active malignancy; (2) acute illness at enrolment; (3) severe psychiatric disorders; (4) substance abuse; and (5) pregnancy or breastfeeding (17). Loss to follow-up is defined as absence from more than two scheduled visits or permanent discontinuation. Follow-up will be maintained through clinic visits supplemented by telephone or electronic contact where necessary.

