Baseline assessment: The project will be carried out from 2025 to 2027 in Gansu Provincial People’s Hospital, Aksay County People’s Hospital, Linxia Prefecture People’s Hospital, Gannan Tibetan Autonomous Prefecture People’s Hospital, and Dingxi City People’s Hospital. High-risk cardiovascular patients of the Han, Hui, Tibetan, and Kazakh ethnic groups will be identified through cardiovascular outpatient clinics, community screening programs, and electronic medical record systems. Follow-Up: it will be conducted at 3, 6, 9, 12, 15, 18, 21, and 24 months after enrollment in the cohort, for a period of 2 years. *Standardized assessment: Demographics, lifestyle, psychology, diet, and medication adherence questionnaires. +Sociodemographic characteristics: Age, sex, ethnicity, residence type, education, occupation, and income. ++Lifestyle factors: Smoking, alcohol consumption, dietary habits, physical activity, and sleep quality. †Clinical history: Hypertension, diabetes, dyslipidemia, previous stroke or TIA, family history of coronary heart disease, and history of drug use. ‡Anthropometry and physiological parameters: Including height, weight, BMI, waist circumference, blood pressure and body fat percentage. **Fasting venous blood tests: High-sensitivity C-reactive protein (hs-CRP), high-sensitivity troponin I (hs-TnI), creatine kinase (CK), creatine kinase-MB (CK-MB), lactate dehydrogenase (LDH), aspartate aminotransferase (AST), soluble suppression of tumorigenicity 2 (sST2), N-terminal pro–B-type natriuretic peptide (NT-proBNP), lipoprotein-associated phospholipase A2 (Lp-PLA2), fasting glucose, insulin, hemoglobin A1c (HbA1c), and a full lipid panel (total cholesterol, low-density lipoprotein cholesterol(LDL-C), high-density lipoprotein cholesterol (HDL-C), and triglycerides. ¶72-h wearable electrocardiogram (ECG) monitoring: A validated clinical-grade device (Shanghai Yishi Technology Co., Ltd.) will be used to continuously conduct 72-h wearable ECG and heart rate variability (HRV) monitoring. The data will be transmitted in real-time to a secure cloud platform, and the NARON CardioAI system will be used for automatic analysis, waveform classification, and feature extractio. ¶¶Transthoracic echocardiography: Unless there are other clinical indications, an echocardiogram will be performed once a year to evaluate the left ventricular ejection fraction and the situation of abnormal wall motion. ***Coronary computed tomography angiography (CCTA): If there are clinical indications should be repeated every 12 months. Assessment Tools: Includes the Rose Angina Questionnaire, The Canadian Cardiovascular Society Angina Classification, The Patient Health Questionnaire-9 (PHQ-9), The Generalized Anxiety Disorder-7 (GAD-7), The Perceived Stress Scale - 10 (PSS-10), The Pittsburgh Sleep Quality Index (PSQI), The Semi-quantitative Food Frequency Questionnaire (FFQ), The International Physical Activity Questionnaire Short Form (IPAQ-SF), The General Medication Adherence Scale (GMAS).

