#### Environmental and contextual data

Environmental variables, comprising monthly averaged meteorological parameters and air pollutant concentrations, were assigned to each patient according to their residential location and the date of hospital admission. Meteorological metrics, such as temperature, precipitation and relative humidity, were acquired from the ECMWF Reanalysis v5 (ERA5) product, which offers global coverage at a 0.25° × 0.25° gridded resolution (approximately 25 km at the equator) (3). For air pollution exposure assessment, concentrations of fine particulate matter (PM2.5 and PM10) (31), ozone (O3) (32), and nitrogen dioxide (NO₂) (33) were derived from the China High-Resolution and High-Quality Near-Surface Air Pollutants (CHAP) Dataset, which provides estimates at a high spatial resolution of 1 km. Elevation above sea level was also incorporated to account for its potential influence on AMI risk across different altitudes.

Healthcare access indicators include average travel time to the nearest secondary or tertiary hospital, hospital bed density, and physician density per 1,000 population (33). Information on socioeconomic factors, including city-level per capita income, employment patterns, occupational classifications, educational attainment, and housing conditions, will be systematically collected during scheduled follow-up visits and cross-referenced with official statistics from the Gansu Statistical Yearbook issued by the Gansu Provincial Bureau of Statistics, China.

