#### Primary outcome analysis

Associations between baseline variables and time to first incident AMI will be evaluated using Cox proportional hazards regression models. Follow-up time will be calculated from enrolment to AMI, loss to follow-up, death, or end of study. Multivariable models will include prespecified variables, including age, sex, ethnicity, smoking status, systolic blood pressure, diabetes status, lipid profile, and environmental exposures. Additional variables will be selected based on clinical relevance. Continuous variables will be modeled on their original scale, and nonlinearity will be assessed using restricted cubic splines. Hazard ratios (HRs) and 95% confidence intervals (CIs) will be reported. The proportional hazards assumption will be assessed using Schoenfeld residuals.

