#### Risk prediction analysis

Prediction models incorporating baseline and time-varying variables will be developed. Candidate predictors will include demographic characteristics, clinical variables, environmental exposures, and repeated biomarker measurements. Predictor selection will be guided by clinical relevance and statistical criteria, including penalized regression methods. Model performance will be evaluated using discrimination and calibration. Discrimination will be assessed using the concordance index (C-statistic), and calibration will be assessed using calibration plots and calibration slope. Internal validation will be conducted using bootstrap resampling.

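### Monthly weather and pollution are dated by hospital admission, which cohort entry does not require, so the exposure date is undefined for some participants and could depend on the outcome

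*Protocol article*

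**What the plan says.** Under Environmental and contextual data, the article describes the exposures as "comprising monthly averaged meteorological parameters and air pollutant concentrations" and says that they "were assigned to each patient according to their residential location and the date of hospital admission". It gives no other dating rule for them.

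The rest of the design is anchored on enrolment:

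- The notes to Table 1 say that participants "will be identified through cardiovascular outpatient clinics, community screening programs, and electronic medical record systems".
- Study population lists "acute illness at enrolment" among the exclusions, and no inclusion criterion requires an admission.
- Primary outcome analysis sets the clock: "Follow-up time will be calculated from enrolment to AMI, loss to follow-up, death, or end of study".
- The same section describes the model: "Associations between baseline variables and time to first incident AMI will be evaluated using Cox proportional hazards regression models". Environmental exposures are among its prespecified covariates.
- Risk prediction analysis uses them too: "Candidate predictors will include demographic characteristics, clinical variables, environmental exposures, and repeated biomarker measurements".
- Analysis of population heterogeneity uses environmental exposure levels as subgroups.
- Longitudinal and short-term risk analysis names only biomarkers and physiological measures as time-updated.

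**The concern.** An index date for exposure should exist for every participant and be fixed without regard to the outcome. Admission meets neither condition here. Many participants found through clinics or community screening may never be admitted during the study, whereas a first AMI will ordinarily lead to an admission.

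Because the exposure is monthly, its date fixes the season and year of the value. If cases take the month of their event and others take some other month, the two groups differ in calendar time before any effect of weather or pollution comes into play. The Cox model for baseline variables would then contain a value from after baseline, and a prediction model could draw on information that is unavailable when a prediction is made. Variation in risk across environments is one of the study's stated aims, so this variable is not a minor adjustment term.

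**Working it through.** **Passages set side by side.** The exposure date is admission. The time origin is enrolment. Entry is by outpatient clinic, community screening or records, with acute illness excluded. Nothing in the article equates admission with enrolment or gives a date for a participant who is never admitted. The mismatch is therefore in the text and needs no calculation. Its possible size does.

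**Inputs from the article.** 2,340 participants, 4% incidence over 24 months, two-sided 0.05.

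**Assumed inputs.** The article gives no exposure variances and no recruitment window beyond a project period of 2025 to 2027. Assumed were:

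- a monthly exposure with mean 35 units and a winter-peaking cosine of amplitude 5, 15 or 25;
- a between-person spatial SD of 5;
- a trend of 0 or -2 units a year;
- a true hazard ratio of 1 and a constant AMI hazard;
- 14.5% attrition, chosen because 2,340 × 0.04 × 0.855 = 80.0, the article's approximate event count. The derivation of that count is in a supplement not shown, and no fault is drawn from it here.

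**Direction by hand.** Put the seasonal peak in January. The mean of the cosine over April to September is (0 - 0.5 - 0.866 - 1 - 0.866 - 0.5)/6 = -0.622. Events spread over 24 months cover two full years, so the seasonal mean for cases is about 0. Cases therefore exceed non-cases by 0.622 × 5 = 3.1, 0.622 × 15 = 9.3 or 0.622 × 25 = 15.6 units with no true effect. October to March recruitment reverses the sign. With even recruitment the seasonal difference is about 0. A trend of -2 a year still leaves about -2 units if non-cases are dated at enrolment, since cases are dated on average 12 months later. It leaves about +2 if non-cases are dated at the end of 24 months.

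**Simulation.** Hazard ratios are per 10 units, with 200 replicates per setting. Ranges cover the three amplitudes and both trends. Cases are dated at AMI throughout.

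| Dating of non-cases | April-September recruitment | October-March recruitment | Rejection rate |
|---|---|---|---|
| Enrolment | 1.47-3.94 | 0.19-0.36 | 52-100% |
| End of follow-up | 1.96-4.14 | 0.38-0.74 | 33-100% |
| Enrolment, but 20% at an admission during follow-up | 1.36-2.04 | 0.34-0.62 | 39-100% |

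With recruitment even over 12 or 24 months:

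- No trend: 0.99-1.03, rejection 1-7%.
- Trend of -2 a year: 0.62-0.96 with non-cases all or mostly dated at enrolment, 1.06-1.64 with non-cases dated at end of follow-up; rejection 9-81%.

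**After correction.** Dating everyone at enrolment gave 0.98-1.03 with rejection of 2-10%. A time-varying exposure, with each risk-set member given the value for their own current date, gave 1.00-1.03 with rejection of 2-3% in four settings of 100 replicates.

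**Second simulation.** With a different exposure model (half the variance seasonal, half between places, per SD) and non-cases dated at enrolment, half-year recruitment gave 2.8-3.3 or 0.36-0.42. Even recruitment gave 0.99-1.10, with up to 14.5% false positives if AMI itself had a winter/summer ratio of 1.5. Under half-year recruitment the null exposure alone reached a C-statistic near 0.69.

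**The case against.** The best defence is that admission is loose wording for arrival at a participating hospital at enrolment. The study calls itself hospital-based, the sentence covers every patient, and the exposures sit in a model of baseline variables. On that reading everyone has the same index date and the bias disappears. This is plausible and cannot be ruled out. It does not rescue the sentence, because the article nowhere defines admission that way and the term does not fit participants found by community screening.

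A reader might infer that the plan dates cases at the event month and non-cases at the enrolment month. The article does not say so. It never mentions event dates in this section, and that split is one way of carrying out a rule that cannot be applied to everyone.

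It is also fair that some non-cases will be admitted. Participants are at high risk, may be up to 85 years old, and are followed for 24 months; record-based recruitment is not confined to outpatients. That admissions would fall mainly to AMI cases is an inference. Giving 20% of non-cases an admission shrank the bias but did not remove it.

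Finally, hazard ratios near 3 or 0.4 need recruitment confined to one half-year, and the article does not describe such a pattern.

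**Conclusion.** The dating rule is wrong as written. It uses an event that cohort entry does not supply, it does not match the time origin, and taken literally it allows the exposure date to depend on the outcome.

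The documents do not establish that the environmental hazard ratios will be biased, or that the prediction model contains future information. Both depend on how the rule is carried out. Under a true null the bias is near zero if recruitment is even over whole years, there is no secular trend and AMI is not itself seasonal. It can be large in either direction if recruitment is clustered by season, and slight to large if there is a secular trend. The article gives neither the recruitment pattern nor the exposure variances, so these figures show a possible range and are not a forecast.

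Only monthly weather and pollutants are at issue. Altitude and the healthcare-access indicators do not depend on this date, so the contrasts in altitude, ethnicity and access between sites stand.

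**What to change.** Replace the admission-date wording with one index-date rule that is the same for cases and non-cases.

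- **Baseline Cox model and baseline predictors:** link each participant's residence to the enrolment month, or to a fixed window ending at enrolment.
- **Short-term analyses:** treat exposure as time-varying. At each event time, give every member of the risk set the value at their own residence for their own current date, with the same lag window for all.
- **Nested case-control analyses:** use the case's calendar date for controls only where risk sets are formed on calendar time, or where controls are matched on calendar date and are under follow-up then. On a clock that starts at enrolment, risk-set members share follow-up time and not calendar date. Imposing the case's date on them could fall outside a member's follow-up, and it would leave only the contrast between places.

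If admission was meant as enrolment, say enrolment. The cost is a change of wording and a different date in the exposure linkage. No new data are needed.

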#### Nested case–control component

Within the cohort, participants who develop incident AMI will be defined as cases, and matched controls will be selected from the risk set. Stored biospecimens from these participants will be used to assess variation in circulating biomarkers as short-term risk indicators prior to AMI, supporting analysis of temporal changes in risk within the cohort.

### Outcomes

The primary outcome is first incident AMI during the 24-month follow-up period. AMI events will be adjudicated according to the Fourth Universal Definition of Myocardial Infarction (2018), based on cardiac biomarker changes together with clinical, electrocardiographic, imaging, and symptom-related evidence. This outcome is defined to capture short-term occurrence of major cardiovascular events within individuals, allowing assessment of variation in near-term risk across populations with different environmental exposures, ethnic backgrounds, and healthcare accessibility.

Secondary outcomes include longitudinal changes in physiological and biochemical indicators, healthcare utilization, and short-term variation in risk markers preceding AMI. Repeated measurements of biomarkers and physiological parameters will be used to evaluate temporal changes within individuals, particularly within the 90 days preceding AMI, to characterize short-term fluctuations in cardiovascular risk. In addition, differences in these trajectories will be examined across environmental and ethnic subgroups to assess population-level heterogeneity in risk patterns.

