#### Follow-up assessments

Participants are followed every 3 months over 24 months using a standardized schedule (Table 1). This repeated-measures design allows assessment of temporal changes in risk indicators and their potential association with short-term cardiovascular events. At each visit, symptom status, interim medical events, medication use, and health-related behaviors are updated. Biomarkers are measured at regular intervals, and ECG monitoring is repeated every 6 months. Echocardiography is repeated annually, and CCTA is performed when clinically indicated. All suspected AMI events are adjudicated by an independent, blinded cardiology panel according to the Fourth Universal Definition of Myocardial Infarction (2018) (21).

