#### Longitudinal and short-term risk analysis

Repeated measurements of physiological and biomarker variables will be analyzed using linear mixed-effects models with random intercepts and random slopes when supported by the data. Time will be modeled as follow-up visit or continuous time since enrolment. Short-term risk will be evaluated using extended Cox models with time-varying covariates. Biomarker and physiological measurements will be updated at each follow-up visit and incorporated as time-dependent variables. For participants with incident AMI, measurements will be aligned relative to the event time. Predefined time windows preceding AMI will be constructed, and values within these windows will be analyzed. Within-individual changes will be defined as differences between consecutive measurements or relative to baseline values. Associations between time-updated variables and AMI risk will be estimated using time-varying Cox models.

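### Individual change within the 90 days before AMI is a stated secondary outcome, but visits about 91 days apart put only one scheduled value in that window, and about half of the windows hold no ECG

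*Protocol article*

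**What the plan says.** Under Outcomes, the secondary outcomes include short-term variation in risk markers before AMI. Repeated biomarker and physiological measurements are to show change within individuals, "particularly within the 90 days preceding AMI, to characterize short-term fluctuations in cardiovascular risk", and these trajectories are then to be compared across environmental and ethnic subgroups.

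The schedule is fixed in the same article. Under Follow-up assessments, "Participants are followed every 3 months over 24 months using a standardized schedule". The notes to Table 1 give the follow-up months: "it will be conducted at 3, 6, 9, 12, 15, 18, 21, and 24 months after enrollment in the cohort". Table 1 marks anthropometry and physiological parameters, fasting blood tests and all questionnaires at each of these visits. For the wearable device, "ECG monitoring is repeated every 6 months".

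Under Longitudinal and short-term risk analysis, "Within-individual changes will be defined as differences between consecutive measurements or relative to baseline values". The same section says "For participants with incident AMI, measurements will be aligned relative to the event time", and then "Predefined time windows preceding AMI will be constructed, and values within these windows will be analyzed".

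The limitations paragraph of the Discussion concedes only that the visit spacing may miss very fast changes just before an event.

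**The concern.** A change needs two measurements. The visit interval is slightly longer than the window in which the change is to be seen, so the schedule normally supplies one value per window. A single value is a level. It cannot show whether the marker rose, fell or fluctuated in the 90 days before the event.

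At stake is how the results will be labelled. The article presents short-term change before a first AMI as its main contribution. If the outcome stays as worded, single levels, or differences reaching back well beyond 90 days, could be reported as 90-day change and then compared between ethnic and environmental groups. The event-aligned windows are also described only for participants who have an AMI. Read on their own, they cannot separate a pre-event shift from ageing, season or visit number.

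**Working it through.** **Inputs from the article**
- Window: 90 days before AMI (Outcomes).
- Visits at 0, 3, ..., 24 months (Table 1 and its notes). With a mean month of 365.25/12 days, the interval is 3 × 365.25/12 = 91.3 days.
- ECG/HRV at 0, 6, 12, 18 and 24 months, an interval of 182.6 days.
- Change needs a consecutive or a baseline value as its second point.
- About 80 expected AMIs (Study population).

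**Assumptions, not in the article**
- AMI times are uniform over 24 months.
- Visit variation of ±7 or ±14 days and 10% missed visits are tried as ranges.

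**The plan's own figure.** 2,340 × 0.04 = 93.6 events. The stated 80 implies a loss of 1 − 80/93.6 = 14.5%. An assumed 15% loss gives 79.6, 10% gives 84.2 and 20% gives 74.9. The article refers to Supplementary Material 1, which is not shown, for this calculation, so the loss allowance is left open. The point does not depend on it.

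**Scheduled values in the 90-day window.** With on-time visits, the chance that a measurement falls in the window is window ÷ interval. Two can fall in it only if the interval is no longer than the window.
- Visits: 90/91.3 = 98.6% of AMIs have one value, 1.4% have none and 0% have two.
- ECG: 90/182.6 = 49.3% have one. The other 50.7%, about 41 of 80, have none. No AMI has two.

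Simulation with the assumed variation gives:

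| Visit variation | Missed visits | No visit value | One | Two | No ECG |
|---|---|---|---|---|---|
| none | 0% | 1.4% | 98.6% | 0% | 50.6% |
| ±7 days | 0% | 3.1% | 95.2% | 1.7% | 50.4% |
| ±14 days | 0% | 5.3% | 90.7% | 4.0% | 50.2% |
| ±14 days | 10% | 13.2% | 83.5% | 3.3% | 54.1% |

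The absence of two on-time values at 91.3-day spacing does not depend on when AMIs occur. The shortest calendar quarter, February to April, has 28 + 31 + 30 = 89 days. It would admit two values only for an AMI within about a day of the second visit.

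**AMIs with no change of any kind.** Those in months 0–3 have only baseline: 80 × 3/24 = 10. For ECG, those in months 0–6 have only baseline: 80 × 6/24 = 20.

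**What can be computed.** A change that starts at an earlier visit and ends inside the window exists for 21/24 × 98.6% = 86% of AMIs. Taken between consecutive on-time visits, it spans about 91 days and starts 91 to 183 days before the event.

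**Look-back that captures both visits.** Among AMIs after month 3, a 180-day look-back holds at least two visits in 97.1% (on time) or 93.4% (±14 days). A 210-day look-back gives 100% or 99.4%.

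**The case against.** The strongest reply is that the article already defines change against the previous visit or baseline, and does not require both values inside the window. About 86% of AMIs then have a change that ends within it, and the Outcomes wording puts emphasis on the 90 days without making them a strict limit. This stands in part: such a change can be computed. But it starts more than 90 days before the event, so it is not the within-window fluctuation that the outcome names.

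Three stronger readings are tempting, and the documents do not support them.
- A reader might infer that nothing can be learned about the last 90 days. Event times are staggered against visits, so in-window values fall anywhere from 0 to 90 days before AMI, and earlier visits anchor each person. In a simulation of 80 cases (uniform event times, between-person SD 1, within-person SD 0.7, linear change from day −90, random-intercept model adjusted for time), a true rise of 0.50 SD was detected in about three of four runs. A mean shift is therefore estimable under a model. An individual's course inside the window is not.
- A reader might infer that cases have no comparator. The article plans risk-set controls (Nested case–control component), conditional logistic regression (Additional analyses) and time-varying Cox models. Only the event-aligned windows are described for cases alone.
- A reader might extend the point to echocardiography. The article nowhere places it in the 90-day outcome. HRV is arguable, because the Discussion counts it among physiological indicators.

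The limitations paragraph does partly admit the issue. It speaks of very rapid change, however, whereas the schedule shows no individual change within 90 days at any speed.

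**Conclusion.** The concern holds for the 90-day wording of the secondary outcome. With on-time visits at 91.3-day spacing no AMI has two values in the window, and about 4% do under an assumed ±14-day variation. About half of the windows hold no ECG, and none holds two. About 10 of 80 AMIs have only a baseline value. These percentages rest on uniform event times, and the visit variation and missed-visit rates are assumptions because the article gives no visit windows.

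The point is limited to this outcome. The baseline Cox analysis of the primary outcome and the time-varying Cox analysis, which carries the latest value forward, do not need two values in 90 days and are unaffected. It should be corrected, but it does not undermine the study.

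**What to change.** - In Outcomes, define pre-event change as the last scheduled value before AMI minus the preceding scheduled value. This is change over about 3 months that starts about 3 to 6 months before the event. A look-back of about 210 days captures both visits for nearly all AMIs after month 3.
- Report the 90-day window as a level only, and leave HRV out of within-window change.
- State that AMIs before month 3 contribute a level but no change.
- In Longitudinal and short-term risk analysis, state that the event-aligned quantities are also computed at the case's index date in the risk-set controls already planned.
- Align the limitations paragraph: the schedule does not show individual change within 90 days, whether rapid or slow.

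The cost is wording and analysis code, with no added visits. The downside is a more modest claim: change between the last two visits before AMI, not change within 90 days.
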